**Figure 6 nutrients-07-05226-f006:**
[figure not shown]
Example of using the mobile food record (mFR) to assess food waste and meat intake. (**a**) Before eating image; (**b**) After eating image.

### 2.4. Outcome Variables

The outcome variables measured using the proposed dietary assessment method include:
number of serves and types of fruit and vegetables and whether they were in season at the time and location of consumption,intake of ultra-processed energy-dense nutrient-poor foods and beverages, separated by type and number of serves,intake of foods and beverages that are individually packaged, separated into “healthy” or “EDNP” foods or beverages,portion sizes and total amount of dairy, eggs and meat productspercentage of plate waste and whether the food wasted was compostable.

### 2.5. Development of Healthy and Sustainable Diet Index

Existing diet quality indices will be reviewed to investigate the processes undertaken in development, validation, and evaluation and will guide the development of the *Healthy and Sustainable Diet Index*. This will be a theoretically driven Index, which will be internally validated using food image data collected during the CHAT study. Each indicator incorporated in the Index will be categorised into one or more of the following elements; impact on human health and/or impact on the environment. For example, ultra-processed EDNP foods and beverages impact health (contributing excess kilojoules and contributing to chronic disease risk) and the environment (use of water, electricity, transport and packaging). Another example is food waste, which has a direct negative impact on the environment (landfill) and a potential influence on health as fresh fruit and vegetables are perishable and often thrown away, creating a barrier for purchase and consumption.

The influence of dietary behaviours on human health will be given the highest weighting, followed by impact on the environment, for example plate waste. Weighting of different food items will involve a thorough assessment of available evidence, including evidence on the life cycle assessment of particular foods (which takes into account green-house gas emissions), and additional effects on ecosystems and biodiversity. The final Index may need to be modified when applied in other countries to take into account differences in the environmental impact of foods produced in various areas and climates, including climate conditions, farming, agricultural and production methods. For example the environmental impact of fruit that requires a climate controlled environment, *versus* seasonal fruit grown outside. A maximum number of total points will be allocated to each component of the *Healthy and Sustainable Diet Index*. A high weighting will not be given to components of the Index that cannot be measured accurately using image-based food records, for example whether fruits and vegetables consumed were locally grown and in season, due to the amount of error.

Each component incorporated into the *Healthy and Sustainable Diet Index*, will be given a weighting used to calculate a final score measuring adherence to a healthy and sustainable diet. For example, typically indices have a maximum score of 100, with a higher score indicating greater adherence to the preferred dietary pattern [23]. Individual components will be given a weighting to reflect consistency with the recommended dietary and sustainable eating outcomes, for example, fruit and vegetable intake may be given a higher weighting as it contributes to both healthy and sustainable eating.

The theoretically driven *Healthy and Sustainable Diet Index* will be internally validated for reliability, content validity and construct validity using 4-days image-based food records collected during a 6-month randomised controlled trial. The baseline data collected during the CHAT study (*n =* 247) will be randomised into thirds using age- and sex-stratified random sample techniques. Two-thirds of the sample will be randomly selected as the derivation cohort and the image-based mFRs of those selected will be used to develop the *Healthy and Sustainable Diet Index* using regression techniques. The remaining one-third of the sample will be used as the validation cohort for the *Healthy and Sustainable Diet Index*. This Index will also be used in the assessment of food images from the 6-month follow up (*n =* 220), and the results compared with baseline.

To assess content validity, components of the *Healthy and Sustainable Diet*
*Index* will be assessed against the Australian Dietary Guidelines [7]. Construct validity will quantitatively assess how well the Index measures conformance to a healthy and sustainable diet.

To determine a total score using the *Healthy and Sustainable Diet Index*, density scores for each component will be calculated. Internal consistency, one form of reliability, will be assessed using Cronbach’s coefficient α. This test has previously been used in the evaluation of the Healthy Eating Index [70] to examine the degree of association between components, to determine if a diet only has one dimension. The relationship between the components of the *Healthy and Sustainable Diet Index* will be assessed using Pearson correlations coefficient. Principle component analysis will be used to assess if there are independent components of the Index. This will measure if there are any significant independent predictors of an overall score.

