## 2. Experimental Section

### 2.1. Study Participants

The study sample to be used for developing the proposed methods will consist of 247 adults aged from 18 to 30 years, comprising of 162 (66%) women and 85 (34%) men previously recruited for another study, the Connecting Healthy and Technology study, referred to as CHAT [26]. Recruitment involved sending letters of invitation to 15,000 residents from 57 suburbs (using the Socio-Economic Indexes for Areas) in the Perth Metropolitan Area from the Federal Electoral Roll, a compulsory enrolment system for Australians aged over 18 years. Participants were screened either online, using a survey website, or on the telephone to ensure the inclusion criteria were satisfied (aged between 18 and 30 years and owned a mobile phone). For the original study, potential participants were excluded if they were: (a) unable to attend on four occasions to complete the 6-month randomised controlled trial; (b) studied nutrition; (c) took part in extreme forms of exercise; (d) followed a restrictive diet; or (e) pregnant or breastfeeding. The CHAT study was conducted between July 2012 and June 2013.

The Connecting Health and Technology study was registered on the Australian and New Zealand Clinical Trials Registry (ACTRN12612000250831) and approved by the Curtin University Human Resources Ethics Committee (HR181/2011) and the Western Australian Department of Human Research Ethics Committee (#2011/90).

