For the development of the proposed methodology, participants completed an mFR at baseline (*n =* 247) and repeated this six months later (*n =* 220). A secondary analysis by the Accredited Practising Dietitian who was involved in the original analysis of all food images collected during the CHAT study will take place. A purpose built Microsoft Access database will be developed to assess the contents of images, and the review of each image pair (including a before and after eating image). A minimum of one image pair per day will be required to be considered a valid day. Five indicators of a healthy and sustainable diet will be assessed using the images captured using the mFR. An objective of this study is to determine whether the five selected dietary behaviours can be assessed from image-based food records without interaction with participants. This is therefore a “proof of concept” approach to developing the Index before replication in possible future interventions. A flowchart outlining the design of the proposed study can be seen in Figure 2.

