## 3. Discussion

The proposed methodologies described in this paper aim to determine if the mobile food record can be used to accurately measure five key indicators of a healthy and sustainable diet. The availability of dietary intake data collected from 4-day mFRs during the CHAT study enables the refinement of the assessment tool and internal validation of a theoretically driven *Healthy and Sustainable Diet Index*. This Index will be tested on a duplicate sample and a longitudinal sample of adults’ 4-day image-based food records to measure content validity, construct validity and reliability.

The *Healthy and Sustainable Diet Index* will be unique in two ways; firstly it will combine the assessment of eating behaviours that influence health outcomes (e.g., EDNP foods and beverages) and dietary behaviours that significantly burden the environment (e.g., ultra-processed foods, food waste). Secondly, it will require the use of image-based food records, which will enable the accurate assessment of dietary behaviours not assessed in traditional forms of dietary assessment (e.g., individually packaged foods).

Using an mFR application to assess the five healthy and sustainable dietary behaviours described in this paper has the potential for further enhancement of the mFR applications capability as a new dietary assessment method. For example, a current fiducial marker probe exists to alert users when the fiducial marker is not located in the image, as described by Ahmad *et al.* [29]. A similar mechanism to ask the user whether food waste detected in the after image was thrown in the rubbish bin, composted, saved for consumption at a later time or other could be incorporated into the mFR application.

Currently there is limited evidence on whether Australian adults have dietary habits consistent with a sustainable diet. Without adequate evidence in this area, appropriate changes to dietary recommendations and nutrition policy are challenging. Results from the Australian Health Survey indicate most Australian’s have eating habits inconsistent with the Dietary Guidelines, contributing to the burden of diet-related diseases in this country [63]. However, to the authors’ knowledge, there is currently no dietary assessment tool or indexing system to assess and monitor whether individuals have dietary behaviours inconsistent with a sustainable diet, such as the use of individual food packaging and plate waste.

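### The protocol must say whether the Index weights are fixed by evidence or estimated by regression; on either reading a single two-thirds/one-third split of 247 people is inefficient, and neither test sample is separate from the original participants.

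*Protocol article*

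**What the plan says.** Section 2.1 sets the sample: "The study sample to be used for developing the proposed methods will consist of 247 adults aged from 18 to 30 years". Section 2.2 says the food record was repeated six months later by 220 of them.

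Section 2.5 gives two accounts of where the Index comes from.

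- Evidence: "This will be a theoretically driven Index, which will be internally validated using food image data collected during the CHAT study". On the weights it adds: "Weighting of different food items will involve a thorough assessment of available evidence". Health impact is to be weighted above environmental impact, and components that images measure poorly are to be weighted low.
- Data: the baseline sample "will be randomised into thirds using age- and sex-stratified random sample techniques". Then: "Two-thirds of the sample will be randomly selected as the derivation cohort", and the records of those selected are used to develop the Index by regression. No dependent variable is named. After that: "The remaining one-third of the sample will be used as the validation cohort for the" Index.

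The same section names Cronbach's alpha, Pearson correlations between components and principal component analysis (PCA), without saying in which cohort they are computed. It also applies the Index to the 220 follow-up records and compares the results with baseline.

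The Discussion (section 3) says: "This Index will be tested on a duplicate sample and a longitudinal sample" of 4-day records.

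**The concern.** A hold-out sample exists to expose optimism, which arises when weights are tuned to the data on which they are then judged. Whether one is needed here depends on whether any weights are estimated, and section 2.5 answers this both ways.

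- **Weights fixed from evidence.** Nothing is fitted and there is no optimism to detect. Keeping about 165 people out of the validation statistics brings no protection.
- **Weights estimated by regression.** A check for optimism is needed. One random split of 247 gives a small test set, an answer that varies with the draw, and a derivation set smaller than the data allow. Resampling corrects for optimism and uses everyone.

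The labels matter as well. The held-out third shares its recruitment with the derivation set (section 2.1), and one dietitian carries out the secondary image analysis for all records (section 2.2). The follow-up records come from the same participants. A reader of the Discussion sentence could credit the Index with more testing than the design provides. The precision and meaning of the Index's reliability and validity figures, a main product of this work, are at stake.

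**Working it through.** **Inputs from the document.** Baseline n = 247 (162 women + 85 men = 247; section 2.1). Follow-up n = 220 (section 2.2). Split two-thirds to one-third (section 2.5). Five indicators (section 2.2). The article states no precision target or sample-size calculation for the validation, so there is no planned figure to reproduce beyond these counts.

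**Assumptions.** The article gives no expected correlation or alpha, so the values of r and alpha below are illustrative and a range is shown. Intervals are two-sided 95%; detectable correlations use two-sided 5% and 80% power.

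**Step 1, size of the split.** 247/3 = 82.3 and 2 × 247/3 = 164.7, so about 82 for validation and 165 for derivation. 165/247 = 67%.

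**Step 2, correlations.** Fisher interval: tanh(atanh(r) ± 1.96/√(n − 3)). For r = 0.30, atanh(r) = 0.310. The half-width is 1.96/√79 = 0.221 at n = 82 and 1.96/√244 = 0.125 at n = 247.

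| Assumed r | n = 82 | n = 247 |
|---|---|---|
| 0.20 | −0.02 to 0.40 | 0.08 to 0.32 |
| 0.30 | 0.09 to 0.49 | 0.18 to 0.41 |
| 0.50 | 0.32 to 0.65 | 0.40 to 0.59 |

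Ratio of standard errors on the Fisher scale: √(244/79) = 1.76. Ratio of interval widths at r = 0.30: 0.397/0.227 = 1.75.

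**Step 3, Cronbach's alpha.** Feldt interval with k = 5: the limits are 1 − (1 − alpha) × F, where F is the 97.5% point (lower limit) or the 2.5% point (upper limit) on n − 1 and (n − 1)(k − 1) degrees of freedom. These are 81 and 324 at n = 82, and 246 and 984 at n = 247.

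| Assumed alpha | n = 82 | n = 247 |
|---|---|---|
| 0.30 | 0.03 to 0.51 | 0.15 to 0.43 |
| 0.50 | 0.31 to 0.65 | 0.39 to 0.59 |
| 0.70 | 0.58 to 0.79 | 0.64 to 0.76 |

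Ratio of widths at alpha = 0.50: (0.653 − 0.306)/(0.592 − 0.394) = 0.347/0.198 = 1.75.

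**Step 4, smallest detectable correlation.** tanh((1.96 + 0.84)/√(n − 3)) = 0.31 at n = 82 and 0.18 at n = 247.

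**Step 5, overlap at follow-up.** 247 − 220 = 27 people have no follow-up record.

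- If all 27 fall in the derivation cohort: 165 − 27 = 138 of 220, or 63%.
- If all 27 fall in the validation cohort: 165 of 220, or 75%.
- If the losses are proportional: 165 × 220/247 = 147.

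A split of 164/83 moves the two limits by one person.

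**The case against.** The strongest reply is that the sentence just before the validation sentence says regression will develop the Index, and the Abstract announces a prediction model. A hold-out then has a purpose. Stratified split-sample validation is a recognised form of internal validation, and section 2.2 calls the work a proof of concept. This stands as far as it goes: the split is not an error of principle if weights are estimated. It remains the less precise option at n = 247, and the article names no outcome for the regression.

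Three stronger readings are tempting, and the document does not support them.

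- A reader might infer that the weights are settled by theory, so that two-thirds of the data are thrown away. The regression sentence contradicts this. On that account the 165 people are used for derivation, and what they are withheld from is validation.
- A reader might infer that the protocol claims an independent or external sample. It does not. It speaks of internal validation in sections 2.5 and 3, and calls the follow-up longitudinal. The loose word is duplicate, which can only refer to the held-out third.
- A reader might infer that every validity figure will rest on 82 people. The text on alpha, correlations and PCA names no cohort, the Discussion also mentions the longitudinal sample, and content validity is a comparison with the dietary guidelines that does not depend on sample size.

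**Conclusion.** The point holds in a limited form and should be acted on, though it does not undermine the study. The article fixes a single random split, and this is a poor choice under either account of the weights. The contradiction between evidence-set weights and regression is the firm part of the finding, because it decides which validation is appropriate.

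The loss of precision is conditional. To the extent that alpha and the correlations are computed in the held-out third only, their intervals are about 1.75 times as wide as with all 247. That ratio is the direct comparison if the weights are fixed. If they are estimated, the direction is the same, but the exact gain from resampling depends on a regression that the article does not specify. The intervals shown rest on assumed values of r and alpha.

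The labelling part rests on counts alone. The duplicate sample is a random third of the same 247 people. Between 63% and 75% of the follow-up participants would be derivation members under the planned split, so the follow-up is not a separate test sample.

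**What to change.** 1. In section 2.5, state whether the component weights are fixed in advance or estimated, and make the rest of the section agree.
2. If fixed: drop the split and compute alpha, the correlations and PCA on all 247 baseline records, with bootstrap 95% intervals.
3. If estimated: name the dependent variable of the regression, repeat the whole weighting step inside each bootstrap sample or each fold of a 10-fold cross-validation on all 247, and report the optimism-corrected figure.
4. In the Discussion, replace the term duplicate sample with a description of internal validation in the same sample. State that the 220 six-month records are repeat measures of the same people. If the split is kept, add that 138 to 165 of them belong to the derivation cohort.

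The cost is rewording, slightly more computing, and a description less simple than a single split. No new data are needed.

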#### 2.3.2. Individually Packaged Foods and Beverages

Food packaging plays a crucial role in maintaining a safe food supply and has the ability to reduce waste by retaining the effect of food processing to extend shelf life [49]. However, food packaging negatively impacts the environment at a number of stages including during production, transport and land fill [15]. Individually packaged foods are convenient and are becoming more common in Australian supermarkets. An Australian study assessed attitudes towards environmentally friendly eating behaviours and found people believe food packaging has a greater impact on the environment compared to the consumption of meat [50].

Key messages in Appendix G of the Australian Dietary Guidelines encourage people to select foods with appropriate packaging and recycle due to the impact on natural resources [7]. Food packaging is not assessed by traditional dietary assessment methods. Images from mFRs show great potential for the accurate assessment of the intake of individually packaged products as they are easily identifiable from the before eating images. Due to the negative impact of packaging on the environment, all individually packaged items will be recorded regardless of the nutrient composition of the food it originally contained. However, individually packaged foods, classified as either EDNP or healthy, will be counted separately to allow for further assessment of adherence to a healthy and sustainable diet. Foods and beverages served from larger packages (so not individually packaged) such as a glass of milk poured from a two litre bottle will not be recorded due to the unavoidable use of larger packages to ensure a safe food supply. A limitation of this method is that some food or beverages may be removed from individual packaging prior to the before eating image being taken. This challenge could be avoided by requesting participants do not remove individual packaging prior to taking images using the mFR.

An example of an image containing individually packaged items collected using the mFR application can be seen in Figure 4. Using the proposed protocol, this eating occasion would likely be assessed as containing two individually packaged EDNP food items and one individually packaged EDNP beverage item.

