#### 2.3.4. Dairy, Eggs and Meat Products

There is substantial evidence supporting the additional environmental impact of meat and dairy foods, compared to plant-based foods [2,14,65]. Along with a growing population and urbanisation, there is a global transition from largely plant-based diets to diets higher in EDNP foods and animal-based foods [45], increasing burden on the food system. While the consumption of dairy foods in Australia is generally below dietary recommended levels, Australians traditionally consume large volumes of meat, with the consumption of beef constituting the highest amount [15]. Meat and dairy products from ruminant cattle and sheep are some of the greatest greenhouse gas contributors in modern diets [8,9].

Previous research in the area of sustainable diets has highlighted a healthy and sustainable diet can be followed without the complete exclusion of dairy and meat [1,2,8,65], however, excessive red meat and processed meat consumption has been linked to an increased risk of colorectal cancer [7,66]. To accommodate this, the latest review of the Australian Dietary Guidelines reduced the standard serving size of lean red meat to a set 65 grams from the previous range of 65 to 100 grams of cooked meat, with a maximum of seven serves, or 455 grams, of red meat per week [7]. In Australia, only 2.1% of people avoid red meat [53]. Therefore, comparing meat intake between small, moderate and large meat consumers is relevant in assessing a healthy and sustainable diet when only a small percentage of the population are vegetarians [67].

When applying the proposed method to this component, food images will be used to estimate average daily intake of milk, cheese and yoghurt, eggs and meat products (including red meat, poultry and fish). The volume of specific types of dairy, eggs and meat products (e.g., beef mince) will be recorded as an approximate gram or millilitre weight and compared to the Australian Dietary Guidelines recommendations [7]. Meat consumed in other food products assessed using this method, such as a beef patty in a commercial burger, will be counted as ultra-processed EDNP food serves and also meat serves.

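### Cronbach's alpha, the only reliability statistic named, is given a purpose it cannot serve, and the component correlations behind it partly reflect counting rules that enter one food in two components

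*Protocol article*

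**What the plan says.** Section 2.5 of the protocol article promises internal validation of the Index for reliability, content validity and construct validity. For reliability it names one statistic: "Internal consistency, one form of reliability, will be assessed using Cronbach’s coefficient α". The support offered is that alpha was used in evaluating an earlier diet index "to examine the degree of association between components, to determine if a diet only has one dimension". Two further component-level analyses follow. Relationships between components "will be assessed using Pearson correlations coefficient", and "Principle component analysis will be used to assess if there are independent components of the Index". Neither is presented as a measure of reliability. The Discussion (section 3) says that the Index will also be tested on "a longitudinal sample of adults’ 4-day image-based food records to measure content validity, construct validity and reliability", without naming a statistic for that purpose.

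The components are defined in section 2.3. Two of the rules let one food enter more than one component:

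- Section 2.3.4, on meat inside other assessed products such as a commercial burger: it "will be counted as ultra-processed EDNP food serves and also meat serves".
- Section 2.3.2, on packaging: "all individually packaged items will be recorded regardless of the nutrient composition of the food it originally contained". Its worked example is an eating occasion with three packaged EDNP items.

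Section 2.5 says that the total score will be built from component density scores. It gives neither the density formula nor the direction in which each component is scored.

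**The concern.** Alpha is a function of the number of components and their average correlation. It carries no information on how many dimensions produce that average, so the purpose cited for it is one it cannot serve.

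The five components were also chosen as different behaviours that together make up the score: EDNP intake, packaging, fruit and vegetables, dairy/eggs/meat, and plate waste. There is no reason to expect them to correlate strongly. Whether they do is a separate question from whether four recorded days place a person stably on the Index. A user of the Index needs the second answer, and alpha does not give it.

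The shared items add a further difficulty. If the same burger raises two components, these correlate even when the underlying behaviours are unrelated. Alpha, the Pearson correlations and the principal components would all pick this up, and nothing in section 2.5 separates it from real association between behaviours.

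**Working it through.** The article states no alpha value, target or sample-size figure for reliability, so there is nothing to reproduce. The number of components, k = 5, comes from sections 2.2 and 2.3. All correlations below are assumptions, shown over a range.

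**Formula.** For standardised components with correlation matrix R, alpha = k/(k−1) × (1 − k/S), where S is the sum of all entries of R.

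**Check 1: can alpha tell one dimension from two?**

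- One factor, all ten correlations 0.24: S = 5 + 2 × 10 × 0.24 = 9.8. Alpha = 1.25 × (1 − 5/9.8) = 0.612. First eigenvalue 1 + 4 × 0.24 = 1.96; the other four are 0.76.
- Two unrelated factors (three components and two), 0.6 within and 0 between: four correlations are non-zero, so S = 5 + 2 × 4 × 0.6 = 9.8. Alpha is again 0.612. The leading eigenvalues are 1 + 2 × 0.6 = 2.2 and 1 + 0.6 = 1.6.

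The alphas are identical, while the eigenvalues separate the two structures. The same holds at other strengths: within-factor correlations of 0.5, 0.7, 0.8 and 0.9 give alpha 0.56, 0.66, 0.70 and 0.74, each matched exactly by a one-factor matrix with the same mean correlation. Conversely, a truly one-dimensional set with mean correlation 0.10 has alpha of only 5 × 0.10/(1 + 4 × 0.10) = 0.36.

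**Check 2: does alpha speak to reproducibility?** If the five behaviours are unrelated across people, S = 5 and alpha = 0. That is true even if every person repeats exactly the same behaviour each day, in which case the score is perfectly reproducible. Alpha therefore cannot stand in for the stability of a 4-day score.

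**Check 3: what can shared items alone produce?** Take independent Poisson counts of item types. Two components sharing a fraction f1 of the first and f2 of the second then correlate at √(f1 × f2). If half of EDNP items are packaged and half of packaged items are EDNP, this is √(0.5 × 0.5) = 0.50. Let a be the induced EDNP–packaging correlation and b the induced EDNP–meat correlation, with all others zero. Then S = 5 + 2(a + b), and the first eigenvalue is 1 + √(a² + b²). It would be 1 with no overlap.

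| a | b | S | alpha | first eigenvalue |
|---|---|---|---|---|
| 0.10 | 0.10 | 5.40 | 0.09 | 1.14 |
| 0.25 | 0.10 | 5.70 | 0.15 | 1.27 |
| 0.50 | 0 | 6.00 | 0.21 | 1.50 |
| 0.50 | 0.29 | 6.58 | 0.30 | 1.58 |
| 0.50 | 0.50 | 7.00 | 0.36 | 1.71 |

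**Direction.** If meat is scored opposite to EDNP, b changes sign. For a = 0.50 and b = −0.29, S = 5.42 and alpha falls to 0.10, while the first eigenvalue stays at 1.58. For a = 0.50 and b = −0.50, S = 5 and alpha is 0. If packaging and meat also share items, with all three induced correlations of size s and meat reversed, S = 5 − 2s. Alpha then runs from −0.05 (s = 0.1) to −0.31 (s = 0.5). Reversing a component does not change the eigenvalues, so uncertainty about direction does not protect the principal component analysis.

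**The case against.** Several replies have force.

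- **The one-dimension wording reports what an earlier index did.** The plan's own description of alpha, as one form of reliability, is narrower and correct. However, the precedent is the only rationale given for using alpha here, so the plan adopts it by implication.
- **Dimensionality is covered.** A reader might infer that the plan rests dimensionality on alpha alone. It does not: the principal component analysis in the same section can separate the structures in Check 1. This reply stands and limits the point to alpha's role.
- **A low alpha would sink the Index.** This is tempting to infer, but no threshold or decision is attached to alpha anywhere in the article.
- **Some foods are counted three times.** A wrapped commercial beef burger would meet the rules of sections 2.3.1, 2.3.2 and 2.3.4 together, but no passage says so. The range of 0.09 to 0.36 uses pairwise overlap only and does not need it.
- **Overlap inflates alpha.** This follows only if the overlapping components are scored in the same direction, which the article does not state. Density scoring may also change the size.
- **The overlap is partly real.** Being packaged and being EDNP are different attributes of one food, and section 2.3.2 already separates packaged EDNP from packaged healthy items. So the double entry is not a scoring error, and forcing each item into one component would change what the Index measures. What stands is that the reader needs to see how much association comes from shared items.
- **A condensed article may leave the longitudinal statistic to a fuller plan.** Agreed; its absence alone is no finding. Baseline-to-6-month agreement would in any case mix real change with unreliability, because a randomised trial lies between the two records.

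**Conclusion.** The point holds in limited form. Alpha is the only reliability statistic named, and it is supported by a purpose it cannot serve: 0.61 arises equally from one dimension and from two unrelated ones. With five deliberately different components, it also leaves the reproducibility of a 4-day score unaddressed. These conclusions follow from the formula and need no assumption about the data.

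The second part is that the counting rules can generate association. The EDNP–meat double count is explicit. The EDNP–packaging overlap follows from the packaging rule and its example. Its size is not known: alpha of about 0.09 to 0.36 rests on assumed induced correlations up to 0.50, unrelated behaviours, pairwise overlap only and scoring in the same direction. With meat reversed, alpha can be near zero or, with packaging–meat overlap added, negative.

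The documents do not support saying that dimensionality goes unexamined, that the Index would be rejected on alpha, or that alpha is necessarily inflated. The change is worth making but is one of analysis and wording, and it does not alter the Index.

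**What to change.** 1. Keep alpha as a description of internal consistency only. Drop the one-dimension purpose and rest dimensionality on the principal component analysis.
2. Add, as the reliability statistic, the intraclass correlation ρ of the Index scored on each of the four date-stamped baseline days, with the Spearman-Brown reliability of the 4-day mean, 4ρ/(1 + 3ρ). State its limits: it covers consecutive Wednesday-to-Saturday days only (section 2.2), treats them as parallel, and says nothing about other days.
3. Report the Pearson correlations, alpha and principal components with and without the shared items, as a sensitivity analysis. Leave the Index scoring unchanged.

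No new data collection is needed. The costs are that by-day scores must be derived once the planned database is built and the weights are set, since they do not exist yet, and that the report gains one extra set of tables.
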